**Methods/design:**

Patients with active thyroid eye disease will be randomised to receive (i) azathioprine *or *oral placebo and (ii) radiotherapy *or *sham-radiotherapy in this multi-centre, factorial randomised control trial. The primary outcome is improvement in disease severity (assessed using a composite binary measure) at 12 months and secondary end-points include quality of life scores and health economic measures.

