### Outcome measures

#### Primary

*1. Binary composite outcome score*:

Treatment success and failure will be defined at study completion (1 year) using a system of major and minor criteria modified from others [8,14,18] (Figure 4).

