**Figure 4 F4:**
[figure not shown]
Binary Composite Primary Outcome Measure.

*2. Ophthalmopathy index *[44]:

Treatment response at study completion (1 year) will also be quantified using the Ophthalmopathy Index (OI) as a continuous measure of disease *severity*.

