#### Co-primary

*1. Clinical activity score *[45,46]:

Short-term response to treatment (3 months) will be evaluated using the Clinical Activity Score (CAS, Table 1) as a continuous measure of disease *activity*.

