### Trial size

#### Number of patients

A two group continuity corrected chi-squared test with a 0.050 two-sided significance level will have 80% power to detect the difference between a success rate in the placebo arm of 60% and success rate in the treated arm of 87% (odds ratio of 4.462) when the sample size in each group is 48. It is therefore necessary for there to be 96 subjects with complete final data sets to be equally distributed to the 4 treatment groups.

The power for continuous outcome measures is more favourable and a total sample size of 100 patients will yield 92% power to detect a difference of 2.7 in the OI with two-sided 5% alpha, assuming a standard deviation of 3.3.

CAS is not considered as important as the primary outcomes in terms of influencing future clinical practice. However it is of greater interest and importance than the secondary outcome variables, and as such it has been selected as a coprimary endpoint and the power of the trial to detect a clinically important difference is presented here. Assuming a standard deviation of between 1.2 and 2.0, a total sample of 100 patients will yield between 71% and 99% power to detect a difference of 1 point with 5% two-sided alpha.

The above power calculations are based on comparisons 'at the margins' of the factorial design (ie, comparing all azathioprine treated patients with placebo treated patients, and all radiotherapy treated patients with sham-radiotherapy treated patients). There will be low power for comparisons between individual cells of the factorial design (eg azathioprine and sham-radiotherapy vs. placebo and radiotherapy), although these analyses will still be conducted to generate pilot data on the comparative efficacy of the 4 combination regimes under investigation.

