### Statistical analyses

Data analysis will proceed according to CONSORT guidelines for randomised controlled trials. The first stage of the analysis will be to use descriptive statistics to describe the group of individuals recruited to the trial in relation to those eligible, and to investigate comparability of the trial arms at baseline. The primary intention-to-treat analyses will comprise comparisons between radiotherapy versus sham-radiotherapy, and azathioprine versus placebo, for each of the two primary outcomes at 12 months follow up. The comparisons will be made using appropriate (that is, logistic or linear) multivariable regression models, adjusting for minimisation variables, the factorial design, and the value of the outcome variable at baseline. Full attention will be paid to the estimates and the confidence intervals for these comparisons as well as the p-values. Secondary analyses will then be conducted using regression models with further adjustment for any prognostic factors that exhibit marked imbalance at baseline. Patients who have no outcome data for the primary analyses will have data imputed using last observation carried forward. Patients who have become non-compliant for any reason will still be invited to produce outcome data such that they can be included in the intention to treat analyses. The assumptions required for the regression models will be investigated using appropriate diagnostic plots, and actions such as transformation of continuous outcome variables taken as necessary.

The co-primary outcome CAS at 3 months follow up, and all secondary outcomes, will be analysed in the same way, using appropriate (linear or logistic) regression models depending on the nature of the outcome measure. Bonferroni corrections for multiple testing will be considered for the secondary outcomes.

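### The Abstract names one primary outcome, but the body tests two for the same 12-month severity claim, each powered at 5%, and mentions multiplicity correction only for secondary outcomes

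*Protocol article*

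**What the plan says.** The Abstract (Methods/design) is in the singular: "The primary outcome is improvement in disease severity (assessed using a composite binary measure) at 12 months".

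Outcome measures lists two items under Primary. The first is the composite: "Treatment success and failure will be defined at study completion (1 year) using a system of major and minor criteria". The second is OI: "Treatment response at study completion (1 year) will also be quantified using the Ophthalmopathy Index (OI) as a continuous measure of disease" severity. A separate Co-primary heading holds CAS: "Short-term response to treatment (3 months) will be evaluated using the Clinical Activity Score".

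Trial size derives the required number of patients from the composite (60% against 87%, two-sided 0.05, 80% power, 48 per group). It then quotes power for OI and for CAS, also at a two-sided 5% level. It places CAS below the primaries and above the secondaries in importance, and says of it that "as such it has been selected as a coprimary endpoint".

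Statistical analyses defines the primary intention-to-treat analyses as the two marginal comparisons, "for each of the two primary outcomes at 12 months follow up". Its one sentence on multiplicity reads: "Bonferroni corrections for multiple testing will be considered for the secondary outcomes".

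**The concern.** Under Objectives, the long-term hypothesis for each intervention is a single statement about severity. The composite and OI both address it at one year, so a significant result on either could be reported as support. The article powers each at the full 5% and attaches possible correction only to outcomes that do not carry the main claim. It states neither an order of testing, nor a split of alpha, nor whether one or both primaries must succeed.

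At stake is what counts as a positive trial. The 5% error rate holds for the composite alone, as the Abstract has it. It does not hold for a claim that either of two measures may establish. Discordant results are quite possible: the Discussion itself says that continuous scores may miss differences that matter clinically, and that composites are weighted towards selected components.

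**Working it through.** **1. The plan's own sample size.** Inputs from Trial size: p1 = 0.60, p2 = 0.87, two-sided alpha 0.05, power 80%, continuity correction. So d = 0.27 and the mean proportion is 0.735.

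- Uncorrected: n' = [1.960·√(2·0.735·0.265) + 0.842·√(0.60·0.40 + 0.87·0.13)]² / 0.27² = (1.223 + 0.500)² / 0.0729 ≈ 40.7.
- Corrected: n = (n'/4)·[1 + √(1 + 4/(n'd))]² ≈ 47.9, so 48 per group and 96 in total.
- Odds ratio: (0.87/0.13)/(0.60/0.40) = 4.46.

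These match the article. The trial is sized on the composite with the whole 5%.

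**2. False-positive chance per intervention, two tests at 5% with either sufficient.**

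- Independent statistics: 1 − 0.95² = 9.75%.
- Upper bound under any dependence: 0.05 + 0.05 = 10%.
- Correlated statistics (one million simulated normal pairs, |z| > 1.96):

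| Assumed correlation | Rate |
|---|---|
| 0.3 | 9.5% |
| 0.5 | 9.1% |
| 0.7 | 8.3% |
| 0.9 | 7.1% |

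The article gives no correlation, so the range is an assumption. Every value exceeds 5%.

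**3. Composite power at 2.5%.** With 48 per group, the continuity correction leaves an effective n' = (48·0.27 − 1)²/(48·0.27²) ≈ 40.9. Power = Φ[(0.27·√40.9 − z·0.624)/0.594].

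- z = 1.960 (5%): Φ(0.846) = 80.1%.
- z = 2.241 (2.5%): Φ(0.551) = 70.9%.

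Keeping 80% power at a fixed 2.5% would need 57 per group, 114 in total.

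**4. OI power at 2.5%.** Inputs from Trial size: difference 2.7, SD 3.3, 100 patients (50 per marginal group), stated power 92% at 5%.

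- Standardised effect: 2.7/(3.3·√(2/50)) = 4.09. Power at 5% is Φ(4.09 − 1.96) = 98.3%, or 98.2% by noncentral t. The stated 92% does not follow from the stated inputs.
- At 2.5%, from those inputs: 96.4% by noncentral t.
- At 2.5%, from the stated 92%: the implied effect is 1.960 + 1.405 = 3.365, and Φ(3.365 − 2.241) = Φ(1.124) ≈ 87%.

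OI power at 2.5% is therefore 87% to 96%, depending on which of the article's figures is right.

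**5. Fixed sequence, composite then OI.** OI is confirmed only when both tests succeed, so its confirmatory power cannot exceed the composite's 80.1%, whichever OI figure is right.

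**The case against.** The strongest reply is that this is a condensed article. The 5% levels stand in the power section, and the analysis section fixes no testing level and stresses estimates and intervals alongside p-values. An order of testing may well be in a full protocol or analysis plan that is not shown. That has force against any complaint of mere silence. It does not remove what the article states: one primary in one place, two in another, and correction mentioned only for the lower tier. A later plan cannot agree with both counts.

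A second reply is that requiring both primaries to succeed would cause no inflation. That is true, but no such rule is stated.

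Two stronger readings are tempting and should not be taken:

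- **Counting CAS as a third chance to win.** With three tests the rate would be 14.3% at correlation 0 and about 11% at 0.7. But CAS measures activity at 3 months and cannot support a claim about long-term severity. Objectives links early remission to radiotherapy only. Trial size ranks CAS below the primaries, and the analysis section counts two primaries without it. What is wrong with CAS is mainly its label.
- **Pooling the two interventions.** Four tests would give up to 18.5% (1 − 0.95⁴). But radiotherapy and azathioprine are separate hypotheses in a factorial design, and a separate 5% for each is commonly accepted. The pooled rate is not the relevant error rate here.

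**Conclusion.** The point holds for the two 12-month primaries. The Abstract and the body contradict each other on the number of primary outcomes, and the body attaches possible correction to the wrong tier. If either primary alone can support the severity claim, the error rate is about 7% to 10% per intervention, an excess of roughly 2 to 5 percentage points over 5%. This rests on three assumptions: each primary is tested at the 5% used for its power, either one suffices, and the correlation lies between 0 and 0.9. The excess is moderate, but it bears directly on what may be declared a success, so it should be settled before unmasking. The document does not support error rates that include CAS or that pool the two interventions.

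**What to change.** Preferred: name the composite as the sole primary outcome for each intervention, tested at two-sided 5%. This agrees with the Abstract and with the calculation that sets 96 patients. Test OI at 5% only if the composite is significant for that intervention. Relabel CAS at 3 months as a key secondary measure of early activity, in line with its lower rank in Trial size, and check that Objectives still agrees, since early remission appears there in the primary radiotherapy hypothesis. No correction between the two interventions is needed.

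Alternative: keep both primaries and apply Holm within each intervention. The smaller p-value is tested at 2.5% and, if significant, the other at 5%.

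Either way, correct the OI power statement, because 92% does not follow from the stated difference, SD and sample size.

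Cost: wording in Outcome measures, Trial size and Statistical analyses, and in the Abstract if two primaries are kept. The planned sample size can stay. Under the fixed sequence, OI cannot be confirmed if the composite fails, which caps its confirmatory power at about 80%. Under Holm, composite power is about 71% whenever it must be tested at 2.5%, and OI power at 2.5% is 87% to 96%. The choice between the two is a design preference; what matters is that one is stated.

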Other secondary analyses will involve: (a) investigation of any interaction between the two interventions for each of the two primary outcomes; (b) pre-planned sub-group analyses to ascertain any differential effects of the interventions according to steroid use versus no steroid use in the six months prior to enrolment. These secondary analyses are readily performed as extensions to the multivariable regression models described above, by simply introducing the appropriate interaction terms. However, the precision of the estimates of interaction is very likely to be too poor, and high p-values will most likely reflect low power and so cannot be taken as evidence for no interactions.

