## Discussion

This randomised controlled trial of azathioprine and radiotherapy (with prednisolone) will be the first to evaluate the role of these interventions as part of a long-term combined immunosuppressive treatment regime for TED. We hope to help resolve the debate which has arisen from recent monotherapy studies [16,55], and seek not only to establish whether the addition of azathioprine or radiotherapy confers benefit in patients treated with glucocorticoids, but also to test the principle of combination therapies in TED.

The use of a factorial design enables us to evaluate two interventions in a single study and is the most valid means of establishing whether the combination of two or more therapies achieves incremental benefits [56]. It also makes efficient use of patients, which is especially important because of the limited numbers of potential recruits with active TED [56,57]. However, in using a factorial design we are assuming (but will have insufficient power to test) that there is no interaction between trial interventions, as if a significant biological or statistical interaction between radiotherapy and azathioprine treatment exists, our calculation of their independent effects will be incorrect. The validity of the study design therefore rests on the judgement of the trial investigators and statistical advisors that the potential for an interaction between our interventions to have a 'clinically significant' effect on the interpretation of the trial data is very low (ie ≤ 5%). We believe this to be a reasonable assertion and consider that the risk of generating uninterpretable data is outweighed by the benefits of using a factorial design to assess combination treatments for an uncommon condition. Our small sample size will also limit our sensitivity to small differences in treatment efficacy, which is a compromise we accept as integral to the conduct of a pragmatic study.

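### The planned logistic interaction test on the binary primary outcome would have no finite maximum-likelihood estimate in about 31% to 49% of trials if both treatments work as planned

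*Protocol article*

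**What the plan says.** The Statistical analyses section prescribes logistic or linear regression for the two primary outcomes, adjusted for the minimisation variables, the factorial design and the baseline value. As secondary analyses it adds the interaction between the two interventions, for each primary outcome, and a subgroup analysis by steroid use in the previous six months. It describes both as "readily performed as extensions to the multivariable regression models described above, by simply introducing the appropriate interaction terms". It then warns that interaction estimates will be imprecise and that large p-values will mostly reflect low power.

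The Number of patients section assumes a "success rate in the placebo arm of 60% and success rate in the treated arm of 87% (odds ratio of 4.462" and asks for "96 subjects with complete final data sets to be equally distributed to the 4 treatment groups", which is 24 per cell. It adds: "The above power calculations are based on comparisons 'at the margins' of the factorial design".

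The Discussion states that "we are assuming (but will have insufficient power to test) that there is no interaction between trial interventions". It concedes that, if a significant interaction exists, "our calculation of their independent effects will be incorrect". It does not give the scale on which no interaction is assumed, or the four cell rates.

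**The concern.** A logistic model with two treatment terms and their product fits the 2×2 table of cells exactly. If one cell has no failures, its fitted log odds is infinite and so is the interaction coefficient. Software may then print a very large coefficient and standard error with a Wald p-value near 1. That output is an artefact and not merely an imprecise result.

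The cell at risk is azathioprine plus radiotherapy, and the risk is greatest when both treatments work. That is also when readers will most want to know how the two combine, and the article promises pilot data on triple therapy. A warning of wide intervals and large p-values presupposes an estimate with an interval, so it does not prepare the analyst for this case. If no method is fixed in advance, the replacement will be chosen after the empty cell has been seen.

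**Working it through.** **Inputs (Number of patients section):** success 60% vs 87%; 48 per margin; 96 patients over 4 cells, so 24 per cell; continuity-corrected chi-squared test, two-sided 5%, 80% power.

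**1. The plan's own figure.** Odds ratio = (0.87/0.13)/(0.60/0.40) = 4.462. Uncorrected n = [1.960·√(2·0.735·0.265) + 0.842·√(0.60·0.40 + 0.87·0.13)]² / 0.27² = 40.7. With the continuity correction, n = (40.7/4)·[1 + √(1 + 4/(40.7·0.27))]² = 47.9, so 48 per group. The stated size reproduces.

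**2. Cell rates with no interaction on the logit scale.** The article does not give them, so two readings are needed.

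- *Reading A:* 60% is the placebo-plus-sham cell and each treatment has odds ratio 4.462. The odds are 1.5, 6.69, 6.69 and 1.5·4.462² = 29.9, giving cells of 60.0/87.0/87.0/96.8%. The margins become (60.0 + 87.0)/2 = 73.5% and (87.0 + 96.8)/2 = 91.9%.
- *Reading B:* 60% and 87% are the margins for both treatments. With x the rate in each single-treatment cell, the other two are 1.20 − x and 1.74 − x. No interaction requires [(1.74 − x)/(x − 0.74)]·[(1.20 − x)/(x − 0.20)] = [x/(1 − x)]², so x = 0.788 and the cells are 41.2/78.8/78.8/95.2%.

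Expected failures in the combined cell are 24·(1 − 0.9676) = 0.78 under A and 24·(1 − 0.9518) = 1.16 under B.

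**3. Chance of no finite estimate** = 1 − Π[1 − p²⁴ − (1 − p)²⁴] over the four cells. Terms not shown below are negligible.

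| Scenario | Cells (%) | Calculation | Chance |
|---|---|---|---|
| A, both work | 60/87/87/96.8 | 1 − (1 − 0.454)(1 − 0.0354)² | 49% |
| B, both work | 41.2/78.8/78.8/95.2 | 1 − (1 − 0.306)(1 − 0.0033)² | 31% |
| One works | 60/60/87/87 | 1 − (1 − 0.0354)² | 7% |
| Both at half the log odds ratio | 60/76/76/87 | 1 − (1 − 0.0354)(1 − 0.0014)² | 4% |

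At 25 per cell, A and B give 47% and 30%; at 22 per cell, 53% and 35%.

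**4. Adjusted model.** The factors in the minimisation table need 14 terms (six binary factors, 4 for centre, 2 for activity, 2 for thyroid status). Simulating 800 trials per scenario, with assumed prevalences and no covariate effects, gave no finite interaction in about 51% (A) and 29% (B). The treatment coefficient in the model without the product term was infinite in 0 to 3%. These figures depend on the assumed prevalences, so the conclusion rests on the exact figures in step 3.

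**5. OI interaction.** The linear model always has an estimate. With the article's SD of 3.3 and 25 per cell (its 100 patients), SE = 3.3·√(4/25) = 1.32, a 95% interval of about ±2.6 points.

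**6. Risk-difference interaction when the logit interaction is zero.** A: 0.968 − 0.870 − 0.870 + 0.600 = −0.17. B: 0.952 − 2·0.788 + 0.412 = −0.21.

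**The case against.** Several counter-arguments have force.

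- *The plan already discounts this analysis.* It is secondary, the article expects poor precision, and it says that large p-values do not show absence of interaction. That removes the main risk of misreading. It does not deal with an estimate that does not exist.
- *A sparse-data estimator is detail for the SAP.* This would be decisive if the article were silent. It is not: it names the model and says that adding a term is enough.
- *The data still carry information.* This is correct. A reader might infer that an infinite estimate says nothing about the interaction, but only the Wald interval is lost. With successes of 14, 21, 21 and 24 out of 24, the likelihood-ratio statistic is 1.08 and the lower 95% profile limit for the interaction odds ratio is about 0.16. Only the upper limit is unbounded.
- *The design does not depend on this test.* A reader might infer that it does from the Discussion's admission that, under interaction, "our calculation of their independent effects will be incorrect". The same paragraph says the trial cannot test the assumption and rests validity on the judgement of investigators and statistical advisors. The stronger inference is not supported.
- *The prior-steroid interaction is less exposed.* It divides margins of 48, not cells of 24. With arms at 60% and 87%, the chance of a cell with no failures is about 7% if half the patients had prior steroids, rising to about 26% if a fifth had. The article gives no prevalence, so both are assumptions.

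**Conclusion.** The concern holds in a limited form. If both treatments have the full planned effect, the stated fit has no finite maximum-likelihood interaction estimate in about 31% to 49% of trials. The lower figure follows the article's statement that its rates are factorial margins. A reader might take about half as the plan's own figure, but that needs 60% to be the placebo-plus-sham rate. The 63–77% glucocorticoid response quoted in the Background gives that reading some support, but the Number of patients section does not say it. If only one treatment works or both effects are halved, the chance is 4% to 7%.

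These figures assume 24 patients per cell and no interaction on the logit scale. They concern one secondary analysis of the binary composite. The OI interaction is unaffected and the main-effect comparisons almost never are. The change is worth making because the article presents the fit as straightforward and the remedy is cheap.

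**What to change.** In the Statistical analyses section, state that the azathioprine-by-radiotherapy interaction on the binary outcome will be fitted by Firth-penalised logistic regression with profile-likelihood confidence limits, and reported with its interval. Keep the treatment terms and as much of the planned adjustment as the data support. At the planned margins only about 48·0.40 + 48·0.13 = 25 failures are expected, against 14 minimisation terms. Present the OI interaction alongside as the more informative of the two. Use the same penalised fit for the prior-steroid interaction if a cell has no failures or no successes.

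A risk-difference interaction can be added only as a descriptive supplement. It asks a different question and would be about −17 to −21 points even with no interaction on the logit scale.

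The cost is about two sentences, with no change to design, data or sample size. The penalised estimate is shrunk slightly towards no interaction, and power stays low.
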